### Deployed measuring instruments

#### Research question 1: The child’s development

##### School performance and specific learning disability

The Basic Diagnostics of Specific Developmental Disorders in Elementary School Age Children (BUEGA; [55]) is an elementary school test battery that aims to measure relevant specific developmental and attention disorders in elementary school children (6–10 years old). It is also possible to use the procedure to evaluate the school achievement potential. Furthermore, an aptitude profile can be created that illustrates the child’s strengths and weaknesses. The BUEGA consists of seven subtests: *Verbal intelligence* (52 items), *Non-verbal intelligence* (38 items), *Expressive language* (57 items), *Reading* (32 items), *Spelling* (10 to 18 items, depending on the grade level), *Arithmetic* (40 items) and *Attentiveness* (strike-through test). The reliabilities for the different scales are between Cronbach’s α = .79 and .96.

##### Mental health

The Child Behavior Checklist (CBCL 6/18 [60]) measures behavioral problems, emotional problems, somatic complaints, as well as social competences of school-age children and youths from their parent’s perspective. The eight syndrome scales (*withdrawn/depressed*, *somatic complaints*, *anxious/depressed*, *social problems*, *thought problems*, *attention problems*, *rule-breaking behavior* and *aggressive behavior*) can be summed up to scales of internalizing and externalizing disorders as well as to an overall sum score. Appropriate internal consistencies of Cronbach’s α > .80 are reported in the German manual [61] for the *total problem score* and the scales *internalizing behavior* and *externalizing behavior.*

When dealing with mental disorders in children and adolescents, the Diagnostic Interview for Children and Youths (Kinder-DIPS; [52]) allows for a diagnosis of mental disorders according to DSM-IV and ICD-10. It encompasses both a parental and a children’s version (for children from the age of 6 years). It allows the assessment of a wide spectrum of current and lifetime mental disorders in children and adolescents: *attention problems*, *activity problems* and *social problems*, *tic disorders*, *anxiety disorders*, *elimination disorders*, *sleep disorders*, *affective disorders* and *eating disorders.* Furthermore, it contains a general clinical-demographic part as well as several screenings (e.g., for *alcoholism*, *drug abuse,* as well as *non-organic psychosis)*. In addition, a psychiatric history, a family history of mental disorders as well as Axes IV (*Psychosocial and environmental problems*) and V (*Global measurement of the level of functioning*) can be assessed. To measure the occurrence of symptoms, the frequency of occurrence or the intensity of a symptom is coded on a 4-point rating scale (*never/seldom* to *very often*, or *never* to *very strong*). For the individual disorder categories, the interrater reliabilities of the parental version (long-term diagnoses) lie between Kappa = .48 (*sleep disorders*) and Kappa = .88 (*affective disorders*). The following modules of the parental version are to be covered within the present study: attention-deficit hyperactivity disorder, anxiety disorders and affective disorders.

#### Socio-emotional development

##### Social competence

The Social Skills Improvement System (SSIS [62]; in a translation by the authors adapted to the target group (forward-backward) makes it possible to measure the social skills of children and youths between the ages of 3 and 18 years. The SSIS instrument consists of several scales to measure three domains: *Social Skills* (subscales*: Communication*, *Cooperation*, *Assertion*, *Empathy*, *Engagement* and *Self-Control*), *Problem Behaviors* (subscales: *Externalizing*, *Internalizing*, *Hyperactivity/Inattentiveness*, *Autism Spectrum* and *Bullying*) and *Academic Competence* (subscales: *Reading*, *Mathematics*, *Motivation*, *Support by parents* and *General Cognitive Function*). In the present study, the domain *Social Skills* will be included as part of the maternal assessment.

##### Aggressiveness

The German questionnaire for aggressive behavior in children (FAVK, “Fragebogen zum aggressiven Verhalten von Kindern” [63]) assesses triggering and maintaining components of aggressive behavior. The external assessment version for parents, teachers and educators will be filled out from the mother. A distinction is made between aggressive behaviors and cognitions toward peers and adults. The FAVK consists of 25 items with a 4-point rating scale on how applicable the behavior is (ranging from *not applicable at all* to *particularly applicable*). Four facets of aggressive behavior are measured: *social-cognitive information processing disorders*, *impulse control disorders*, *social skills disorders* and *social interaction disorders*. The internal consistency of the questionnaire ranges between Cronbach’s α = .92 and .95.

##### Psychopathy

The Inventory of Callous-Unemotional Traits (ICU) [64] measures callous, cunning and hard-hearted qualities and is based on the *Callous Unemotional* scale of the APSD. The ICU consists of three scales: *Callousness, Uncaring* and *Unemotional* and contains a total of 24 items. The teachers are to assess the occurrence of behaviors by children on a four-stage scale (*not at all true* to *definitely true*). The documented internal consistency of the ICU is between Cronbach’s α = .64 and .77.

##### Life satisfaction

To measure the life quality of children and youths a German inventory is administered (“Inventar zur Erfassung der Lebensqualität bei Kindern und Jugendlichen”, ILK [65]). Life quality is divided into different areas that are measured separately: *school*, *family*, *social contact with peers* and *interests and recreational activities.* Furthermore, there are two health-related topics: *physical health* and *mental health*. In addition to the individual areas, an overall assessment of quality of life is possible. The entire self-assessment version of the ILK (apart from the health-oriented areas) is to be used when interviewing the child. Seven items are thus presented with an answer format suitable for children (Smiley symbols). The internal consistency of the life quality scores for children and youths range between Cronbach’s α = .55 and .63.

#### Children’s preferences

##### Pro-social behavior

The game regarding interpersonal allocation decisions [57] consists of four rounds. In each round, the child can choose between an egalitarian allocation and an alternative where the child gains an advantage or disadvantage over other imaginary children. In the *pro-social decision situation*, the child can choose between the allocation (1–1), which means 1 point for the child and 1 point for the imaginary other children, and the allocation (1–0). This allocation allows the child to distribute a point to the other imaginary children without additional costs. In the *cost-incurring pro-social decision situation*, the child is to choose between a (1–1) and (2–0) allocation. The child can only increase their own payment at the expense of the imaginary children. In the *envy decision situation*, the child chooses between the allocation (1–1) and (1–2), which makes it possible for the child to reduce the payment to the imaginary children without incurring any costs of their own. In the *cost-incurring envy decision situation* the child chooses between the allocation (1–1) and (2–4), which leads to a reduction of the payment to the imaginary children that incurs costs of their own.

##### Risk behavior

The game *Investment decision in a lottery* [56] measures the child’s willingness to take risks. Before each round the child can bet between zero and five points in a lottery, in which they can double their points with a probability of 50% or lose the points they have bet with a probability of 50%. Points that are not bet are safe for the child. The number of points that are bet can be regarded as a measure of the child’s willingness to take on risk.

##### Time preference

The game regarding *temporary allocation decisions* [58] makes it possible to assess the child’s individual time preference. In this game, the child can choose whether they want to immediately receive the points won in the previous game, exchange them for a present or continue to collect further points by deciding to receive the present at a later point in time. The child receives 2 points for every week that they waits. The child can wait for a maximum of 4 weeks. The number of weeks can be regarded as a measure of the individual time preference.

### Research question 2: Dysfunctional parenting behavior, child abuse and child neglect

#### Dysfunctional parenting behavior

The Parenting Scale (PS [66] in a translation by the authors adapted to the target group (forward-backward)) measures dysfunctional disciplinary parenting behavior. Based on examples of children’s behavior, the parents are to classify their own behavior ranging between *functional* and *dysfunctional*.

#### Child abuse

The Parent-Child Conflict Tactic Scales (CTS-PC [67] in a translation by the authors adapted to the target group (forward-backward)), is a parent-child version of the CTS that measures psychological and physical abuse and neglect, as well as non-violent disciplining of children by their parents. The instrument contains 35 items and can be used when interviewing the mother, whereby she rates her own behavior toward her child. The CTS-PC is composed of the subscales *nonviolent discipline*, *psychological aggression*, *physical assault*, *neglect*, *weekly discipline* and *sexual abuse*.

The CTS-PC, Child Report assesses conflict resolution strategies in family or close relationships as rated by the children. In line with the parent-version, the child version measures psychological and physical abuse and neglect, as well as nonviolent disciplining of children by their parents. It is designed for 6- to 9-year-olds. It operates with pictures that describe conflict situations in the family that the child may possibly recognize. The pictures depict different levels of severity, whereby only the three dimensions non-violent discipline, psychological aggression and minor physical assault are used in the present study. A psychometric evaluation of the adapted German version of the CTS-PC was recently conducted by the AMIS (analyzing pathways from childhood maltreatment to internalizing symptoms and disorders in children and adolescents) study of the University of Leipzig [68].

#### Child neglect

The Multidimensional Neglectful Behavior Scale (MNBS [69]; German version translated for the AMIS study of the University of Leipzig) assesses various forms of parental behavior regarding child neglect. There are various versions of the MNBS, and all of them measure the extent to which the following needs of a child have been neglected: *Physical needs* (e.g., food and clothing), *emotional needs* (e.g., affection and support), *supervisory needs* (e.g., taking an interest in the child’s misconduct and knowledge about their whereabouts) and *cognitive needs* (e.g., reading out loud or helping with homework). The MNBS exists, among other versions, as a self-report for parents and children aged 0–15 years (Form P/PS). This version is to be used when interviewing the mother. With its 38 items, it measures her neglectful behavior when raising her child. Furthermore, within the present study, a picture-based children’s version is presented. The picture cards are thereby shown to the child, who chooses situations that are applicable to their everyday family life. The children are presented with the three scales *emotional neglect, cognitive neglect* and *supervisory neglect*.

### Research question 3: Maternal mental health

#### Stress

The short form of the Depression-Anxiety-Stress Scale (DASS-21 [70]; a translation adapted to the target group (forward-backward)) serves to assess the frequency (*never* to *very often*) of negative emotional states during the last 4 weeks. The DASS-21 contains three dimensions: *depression* (e.g., dysphoria and hopelessness, *anxiety* (e.g., autonomic arousal and situational anxiety) and *stress* (e.g., chronic, non-specific arousal and irritability).

#### Psychopathology

The DIA-X [51] is a fully structured diagnostic procedure to measure mental disorders based on ICD-10 and DSM-IV criteria. The interview is a modified form of the CIDI (Composite International Diagnostic Interview) from the World Health Organization (WHO). The DIA-X makes it possible to survey more than 100 mental disorder categories. It gathers data on *organic mental disorders*, *substance disorders*, *affective disorders (manias, hypomanias, depressive disorders)*, *anxiety disorders*, *obsessive-compulsive disorders*, *reactions*, *dissociative disorders*, *somatoform disorders* and *eating disorders.* Lifetime as well as acute diagnoses can be obtained. The DIA-X is divided into 16 sections. Due to the possibility of selecting and presenting individual sections of the interview, an adapted interview that focuses on specific disorders can be carried out. The instrument comprises four DIA-X screening questionnaires: one stem screening questionnaire, which contains all 16 stem questions in the DIA-X interview, an anxiety screening questionnaire, a depression screening questionnaire, and a questionnaire regarding premenstrual syndrome. These questionnaires make it possible to assess whether it is any indication to conduct the entire DIA-X interview. The interrater reliabilities are specified as being between the values of Kappa = .81 to 1.0.

#### Social support

The short form of the questionnaire regarding perceived social support (FSozU-K 6 [71]) measures the social support as perceived or anticipated support from the social environment. The items are in the form of statements, whereby the participant specifies their level of agreement on a 5-point scale (*not at all true* to *absolutely true)*. The internal consistency of FSozU-K6 was found to be Cronbach’s α = .90.

#### Stress due to parenting tasks

The Parenting Stress Index (PSI) [72] (German version: Eltern-Belastungs-Inventar, EBI [73]) assesses whether parents, due to an increased level of stress, are impaired regarding their care and support of their child. The EBI contains a total of 48 items that are answered on a 5-point Likert scale (*absolutely true* to *not true at all)*. The internal consistency of the EBI overall scale amounts to Cronbach’s α = .95.

### Partnership

#### Partnership satisfaction

The short form of the partnership questionnaire (PFB-K; [74, 75]) assesses the satisfaction in a partnership or marriage with the help of nine items. Three items can be allocated to each of the three subscales *fighting behavior, tenderness* and *commonality/communication*. Within a representative population survey, an internal consistency of Cronbach’s α = .84 (women: Cronbach’s α = .87; men: Cronbach’s α = .81) was determined for the overall value of the PFB-K.

#### Partnership violence

The Conflict Tactics Scales (CTS2) [54] translation adapted to the target group (forward-backward)) serves to assess conflict resolution strategies within the family or close relationships. The CTS2 (revised and modified version of the CTS) measure three forms of conflict handling: *negotiation* (six items), *psychological aggression* (eight items) and *physical violence* (12 items). In addition, it measures *sexual coercion* (seven items) and *injuries caused by violence by the partner* (six items). With the help of CTS2, information is collected about one’s own behavior as well as that of the partner. The latter is relevant to the present study.

#### Partnership stability

The items assessing partnership stability document the marital status of the participant (unmarried, married, widowed or divorced). Additionally, the participants are asked for household composition, whether she is in a partnership and whether the partner is the biological father of the treatment child.

#### Self-efficacy

The Parenting Sense of Competence Scale (PSOC [76] translation adapted to the target group [forward-backward]) measures the experience of competence in the role as parent on two dimensions: *satisfaction* and *efficacy.* The dimension *satisfaction* comprises nine items and includes *parental care, motivation* and *frustration.* The dimension *efficacy* measures *parental competency, performance* and *problem-solving ability* with the help of seven items. The 16 items are presented as statements and assessed on a six-point Likert scale (*strongly disagree* to *strongly agree*).

#### Life satisfaction

The German Version of the Life Satisfaction Questionnaire (“Fragebogen zur Lebenszufriedenheit”, FLZ [77]) serves to measure relevant aspects of life satisfaction in ten areas of life (*health, work and career, financial situation, recreation, marriage and partnership, relationship with one’s children, own self, sexuality, friends/ acquaintances/ relatives* and *housing*). Each subscale comprises seven items, which are assessed on a 7-point rating scale (*very dissatisfied* to *very satisfied*). The questionnaire can be used from the age of 14 and will be used when interviewing the mother. In addition to measuring the area-specific life satisfaction, the FLZ allows for the assessment of the general life satisfaction, which is calculated as the sum score of seven of the ten scales. The internal consistency for the overall value are satisfactory (mothers α = .74; fathers: α = .76). The FLZ was standardized via a representative German sample, hence norms are available for various age and occupational groups.

### Research question 4: The families’ socio-economic situation

#### Family income, employment and education

Different scales from the German Socio-Economic Panel (SOEP) [49] were used to asses family income, employment rates and educational status. The German SOEP study (GSOEP) is conducted by the *Deutsches Institut für Wirtschaftsforchung* (DIW – German Institute for Economic Research). It was initiated in 1984 and has been conducted annually since then.

#### Acceptance of employment, training or educational offers

A five-item scale used in the SOEP [49] as well as in the *Panel Labor Market and Social Security* (PASS [78]) was used to measure employment attitudes. These questions contain certain statements about the importance of employment for the individual to which the participant can completely agree or completely disagree. Additionally, a six-item scale used in the SOEP and PASS assesses acceptable obstacles regarding the start of an occupation. The respondents can rate these difficulties on a 4-point Likert scale from *I will accept in any* case to *I will not accept in any case*.

#### Welfare payments

The Research Data Centre (FDZ) of the Federal Employment Agency at the Institute of Employment Research (IAB) provides social security data (Integrated Employment History) for all participants. The participating individuals will be identified by the participants’ name, date of birth and address from the social security data. For all participants who are identified via their social security data, it is possible to merge survey and assessment data with their welfare receipt spells, amount of welfare, and additional cash transfers. Additionally, the social security data provides employment spells, wage spells and indicators about the type of occupation. The data is available from the participant’s entry into the labor market until the time of the follow-up data collection.

#### Family situation

The Home Observation for Measurement of the Environment (HOME [59] forward-backward translation by the authors) assesses the lifestyle and living situation within a family. As an external evaluation, following the home-visiting, the interviewer reports whether, based on yes-no answers, certain circumstances (e.g., regarding the apartment) or behaviors (e.g., regarding the interaction with the child) could be observed in the family or not. *Yes* identifies the existence and *No* the non-existence of the circumstance or behaviors specified by each item. Depending on the age of the children, the HOME consists of 45 to 60 items. The subscales also vary depending on the version. The HOME exists in four versions for the assessment of the living situations of children of different age groups. Due to some questionable items (e.g., negative rating for the lack of a television), the items were culturally adapted to the German-speaking area as well as to family life in the 21st century in general.

### Research question 5: Health and health service utilization of mother and child

#### Mother’s physical health

The 12-item Short Form Health Survey (SF-12 [79]) is an outcome-oriented, subjective measure of physical and mental health. It includes 12 items. Ten items are assessed on a 5-point Likert scale asking how often (*always* to *never*) different physical and mental stresses and strains are absent or present in the previous 4 weeks. Additionally, two questions assess whether the health status decreases (*strongly*, *a little bit, not at all*) the ability to climb stairs and lift. Anderson et al. [79] show that the SF-12 is a suitable instrument to conduct health economic quality of life calculations. As the SF-12 is widely used in other panel surveys, it provides the possibility for external validation of the participant’s responses.

#### Child physical health and health service utilization

The German Health Interview and Examination Survey for Children and Adolescents (KiGGS) questionnaire [80] assesses accidents which lead to outpatient or inpatient care in the last 12 months before the survey. In the case of an accident, the location and the type of the accident are inquired of, as well as the injury sustained. For all these questions standardized answers are presented. Furthermore, the KiGGS questionnaire inquires the frequency of certain diseases as well as the utilization of certain health care services. An alternative source for the assessment of pediatric primary care usage (e.g., screenings, vaccinations) is the evaluation of health insurance data. For those participants who declared consent, data can be merged to the participants by the individual health insurance number. With the help of the International Statistical Classification of Diseases and Related Health Problems (ICD) code, it is possible to identify the date and frequency of pediatric primary care utilization.

#### Number of injuries

The health insurance data can also be used to identify injuries that lead to a hospital admission or physician visit. All injuries and intoxications are coded S and T in the ICD systematic. Due to the health insurance data, it is possible to identify the date of the injury, the duration of treatment and which follow-up treatments are needed which can serve as a proxy for the severity of the injury.

### Data analysis

The primary and secondary analyses will be conducted on an intention-to-treat basis. Multilevel modeling will be used for statistical analyses of our primary and secondary outcomes. Prior to analysis, data will be checked for outliers, inconsistencies and possible transformation. We predict that our sample size will be large enough for our statistical tests to be robust regarding non-normally distributed variables. To reduce bias and loss of statistical power in our analysis of primary and secondary outcome indicators, we will use multiple imputations to estimate values for missing data. Power analyses (i.e., *sensitivity*) based on an attrition rate of 30% (*N* = 542 for the CATIs, CAPIs and developmental tests) given a type I error rate (false positive) of α = .05 and statistical power of 1− *β* = .80 resulted in a minimum detectable effect sizes of ES = 0.2. For an attrition rate of 40% (*N* = 465) a minimum detectable effect sizes of ES = 0.23 was estimated. To take that into account we analyze different outcome measures within one hypothesis, we will adjust our results for multiple hypothesis testing (MHT) to control the family-wise type I error rate.

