### NFP in Germany: The “Pro Kind” study

In Germany, within the framework of the model project Pro Kind, a German adaptation of the NFP program has been scientifically evaluated since 2006. The core components of the NFP interventions were implemented by the Pro Kind program without changes, including the target group criteria, the specified average number of visits and the average duration of a visit. Furthermore, the structured procedure as well as the support for the home visitors through supervision accord with the US original. Modeled after the NFP program, the home visitors conducted the visits regularly, from pregnancy to the child’s second birthday. Diverging from the original program, in the German adaptation home visits were carried out by social workers and state licensed midwives either alone (mainly midwives) or in tandems of a midwife and a social worker (see [42]), whereas in the NFP program exclusively nurses were engaged as home visitors.

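### The stated detectable effects (0.2 and 0.23) carry no allowance for clustering by home visitor in the treatment arm, although multilevel analysis is announced

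*Protocol article*

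**What the plan says.** The Data analysis section of the protocol article names the model family, for primary and secondary outcomes alike: "Multilevel modeling will be used for statistical analyses". It names no level. The same paragraph then gives the sensitivity of the follow-up:

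- inputs: a "type I error rate (false positive) of α = .05", with sidedness not stated, and power given as "statistical power of 1− *β* = .80";
- first scenario: "attrition rate of 30% (*N* = 542 for the CATIs, CAPIs and developmental tests", which "resulted in a minimum detectable effect sizes of ES = 0.2";
- second scenario: "For an attrition rate of 40% (*N* = 465) a minimum detectable effect sizes of ES = 0.23 was estimated".

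No ICC, number of clusters or design effect accompanies these figures.

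On delivery, the section on NFP in Germany says that "home visits were carried out by social workers and state licensed midwives either alone (mainly midwives) or in tandems"; each tandem paired one midwife with one social worker. Under Sample and sampling, mothers were randomised individually, with implementation location as one of the strata, and both groups had access to regular welfare support. No programme visitor is described for the control group. Under Program participation, visits per family ranged from 0 to 94.

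**The concern.** Families served by the same midwife, social worker or tandem share that person's skill and style, so their outcomes may be correlated. Control families have no such link. The trial is therefore individually randomised with possible clustering in one arm only. A grouping that exists in both arms, such as location, does not represent it.

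The detectable effect tells a reader what a null result at age 7 to 8 would rule out. If it is calculated for independent families while the announced analysis allows for clustering, it promises more sensitivity than that analysis can deliver. The planning effect is only 0.20, so a modest loss matters.

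**Working it through.** **Inputs from the article:** alpha 0.05, power 0.80, N = 542 and N = 465 (775 × 0.70 = 542.5; 775 × 0.60 = 465), allocation about 1:1.

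**Inputs not in the article (assumed):** m = 7 to 17 followed-up treatment families per visitor, ICC 0.01 to 0.05. With 542/2 = 271 treatment families, this implies about 39 down to 16 visitors.

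**Step 1: reproduce the plan's figures.** For two independent means with SD 1 and equal arms, the detectable effect is (z_alpha + z_0.80) × √(4/N).

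| N | One-sided: (1.645 + 0.842) × √(4/N) | Two-sided: (1.960 + 0.842) × √(4/N) | Printed |
|---|---|---|---|
| 542 | 0.214 | 0.241 | 0.2 |
| 465 | 0.231 | 0.260 | 0.23 |

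The one-sided value matches at N = 465. At N = 542 it matches only when rounded to one decimal; power at exactly 0.20 is 75.3% one-sided. Neither two-sided value matches: power at the printed effects is 64.4% (N = 542) and 69.8% (N = 465).

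The original sample size points the same way. One-sided, ES 0.20 with independent observations needs 620, and 620 × 1.25 = 775, the planned N under Sample and sampling.

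**Step 2: add clustering in one arm.** The variance of the treatment mean is multiplied by DE = 1 + (m − 1) × ICC and the control mean is unchanged. With equal arms and equal total variance, the standard error of the difference is multiplied by √((DE + 1)/2).

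| Assumption | DE | SE factor |
|---|---|---|
| m = 7, ICC 0.01 | 1.06 | √(2.06/2) = 1.015 |
| m = 12, ICC 0.02 | 1.22 | √(2.22/2) = 1.054 |
| m = 17, ICC 0.05 | 1.80 | √(2.80/2) = 1.183 |

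**Step 3: restated detectable effects** (Step 1 value × SE factor).

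| N | Two-sided: low, middle, high | One-sided: low, high |
|---|---|---|
| 542 | 0.244, 0.254, 0.285 | 0.217, 0.253 |
| 465 | 0.264, 0.274, 0.307 | 0.234, 0.273 |

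A wider assumed range (m = 5 to 20, ICC 0.01 to 0.10) gives 0.243 to 0.336 at N = 542 and 0.262 to 0.363 at N = 465, two-sided. These are normal approximations, which take no account of the small number of visitors.

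**Step 4: separate clustering from sidedness.** Moving from one-sided to two-sided multiplies the detectable effect by 2.802/2.487 = 1.127. That is about the effect of m = 10 with ICC 0.06: DE = 1.54, factor √(2.54/2) = 1.127. The step from 0.214 to 0.241 is therefore sidedness alone; only the step from 0.241 to 0.244–0.285 is clustering.

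**Step 5: type I error, only if the analysis ignored visitors.** The two-sided error would be 2 × (1 − Φ(1.96/factor)): 5.3% at the low end, 6.3% in the middle and 9.8% at the high end.

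**The case against.** **The model may already include the visitor.** The levels are unnamed, nothing excludes home visitors, and an article may leave the random-effects structure to a fuller document. This stands. A reader might infer that the trial's standard errors will be too small and its type I error inflated. The article does not support that, because the percentages in Step 5 apply only if visitors are ignored. They also need a particular null. If the programme affects no family, the choice of visitor cannot matter and no one-arm clustering arises. Inflation requires visitor effects that are non-zero but average to zero, with visitors treated as a sample from a wider population.

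**The size is assumed.** This also stands. At the low end, 0.241 becomes 0.244, which is negligible. A small ICC is plausible: outcomes are measured about 6 years after the programme ended, 42.2% of the treatment group left the programme early, and some families had no visits. That several families shared a visitor is itself an inference, since the number of visitors is not given.

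**The match in Step 1 is not unique.** A two-sided calculation with covariates explaining about 22% of the variance would give 0.230 and 0.213. The article mentions no covariates beside these figures, and that reading contains no design effect either.

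**A partially nested model does not rescue power.** Correct. A reader might infer that choosing the right model makes the printed figures valid. It protects the standard errors, but the detectable effect has to be restated whichever model is fitted.

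**Conclusion.** The point holds for the printed detectable effects. They are met by an independent two-sample formula, read one-sided, and state no clustering allowance, while the same paragraph announces multilevel analysis and only the treatment arm has programme visitors. If visitors served several families, any positive visitor ICC makes 0.2 and 0.23 too favourable. The direction is clear but the size is not known from the article. Under the assumed 7 to 17 families per visitor and ICC 0.01 to 0.05, the detectable effect rises by 1.5% to 18%, to 0.244–0.285 at N = 542 and 0.264–0.307 at N = 465, two-sided. The unstated sidedness accounts for a further gap of about 13% that has nothing to do with clustering. Misleading error bars are not shown; they remain a risk if visitors are left out of the model.

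**What to change.** 1. Restate the detectable effect at both values of N, give its sidedness, and show it over a range of visitor ICC using the actual number of visitors and families per visitor.
2. Include home visitor or tandem as a random effect in the treatment arm only, with controls and treatment families who received no visits as singletons, and location as a fixed effect. If visitors worked in more than one pairing, use a multiple-membership structure.

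The cost is a few sentences of analysis wording and a visitor identifier from programme records, whose availability the article does not mention. The downside is slightly wider intervals and a less favourable stated figure.
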